attend clinic visits every twelve months. If they will be unable to come to the clinic, home or institutional visits as well as phone contacts might be scheduled. Telephone or proxy interviews will be scheduled if in-person visits cannot be completed. Attendance at scheduled visits will be documented by completion of specific data collection forms. Study centres are advised to keep detailed records of rescheduled and broken appointments for each participant. Participant retention will be monitored, and efforts will be made to identify those individuals who need support and encouragement. Records of participants consenting to only a portion of the follow-up procedures, i.e., partial compliance, will also be maintained. Summary reports of such difficulties will help identify problems. Critical review of such problems may offer potential solutions.

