### 10. Sample size considerations and statistical analysis

#### 10.1. Sample size considerations

The primary efficacy endpoint is the time from randomization to the date of first occurrence of inability to complete the 400-m walk test in less than 15 min.

Sample size calculation is based on the LIFE study database. Specifically, survival analyses were run according to different baseline levels of SPPB score (lower than 8 vs. 8 and 9) for the primary endpoint. As depicted in Fig. 6, the effect of a long-term structured PA programme on major mobility disability was negligible in participants with baseline SPPB score  $\geq 8$  (hazard ratio = 0.94). Conversely, the hazard ratio was clinically and statistically significant in enrollees with baseline SPPB  $< 8$  (hazard ratio = 0.75; 95% CI [0.59;0.94];  $p=0.012$ ).

A total of 434 events are required to provide 85% power to detect a 25% reduction in the hazard of major mobility disability using a log-rank test performed at a two-sided alpha level of 5%. In order to achieve the 434 targeted events, 1200 subjects with baseline SPPB  $< 8$  will need to be randomised over a 12-month accrual period, with a maximal follow-up time of 3 years and a common exponential dropout rate of 25% over two years. The inclusion in the SPRINTT RCT of participants with a baseline SPPB score of 8 and above would decrease the study power and, hence, the probability of success of the trial. On the other hand, restricting the enrolment to older people with SPPB  $< 8$  would limit the aim of study to characterise the whole spectrum of PF&S. Hence, a convenience sample of 300 older adults with baseline SPPB 8 or 9 will be included in the study. An ad hoc hierarchical testing procedure has been formulated to preserve the study power (see below).

Three different plans have been developed, based on recruitment efficiency, incidence of events and length of follow-up. A blinded sample size reassessment based on number of events is planned after 11 months from the beginning of recruitment to ensure that 434 events will be reported at the end of study (3 years after the first study participant has been enrolled). This interim evaluation will allow taking immediate actions to preserve the study power in case the efficiency of enrolment or the number of observed events is not coherent with the original assumptions.

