### **Derivation of primary endpoint**

Disability will be considered ascertained:

- at the date of the 400-meter walk test, if participants fail to walk 400 meters within 15 minutes, or need an assistive device
- or at the date of the visit (or date of the 400-meter walk test if available) when the visit is performed but the participant did not perform the 400-meter walk test and the adjudication (automatic or from the committee) does not classified the event as no disability (i.e. ascertained or not conclusive) if any

- or at the date of death if the participants died during the study

Participants who have not met this disability criterion at the end of their study participation (including withdrawals) will be considered as right-censored observations. The censoring time will be calculated as the date of their last successful completed 400-meter walk test (including assessment of “no disability” by the automatic adjudication or the adjudication committee) minus the date of randomization visit V1-T0 (or date of randomization if V1 is missing) + 1 day.

**Particular cases:** In the case where more than 9 months are observed between two consecutive visits or between the last available visit and the death:

- If the disability criterion is not met at the 2nd consecutive visit, then participants will be censored at the date of their first consecutive visit. In the case where the first of the two consecutive visits is the randomization visit, then the censoring time will be equal to 1.
- If the disability criterion is observed at the 2nd visit of the two consecutive visits, or the participant died more than 9 month after the last available visit, then the disability will be considered ascertained at the date of the first consecutive visit or at the date of the last available visit before to die, plus 183 days (i.e., 6 months). In the case where the first of the two consecutive visits (or the last available visit before to die) is the randomization visit, then the disability will be considered ascertained at the date of randomization visit V1-T0 (or date of randomization if V1 is missing) + 183 days.

If no post-baseline visit is done, then participants will be censored at the date of randomization visit V1-T0 (or date of randomization if V1 is missing).

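### The nine-month gap rule lets the later walk result decide who is censored, so the primary hazard ratio is unbiased only if wholly missed visits are balanced between arms

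*Combined protocol and SAP*

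**What the plan says.** The walk test is scheduled at month 3, month 6 and then every six months (SAP 2.1.3.1 and the visit table). The general rule in SAP 2.1.3.1 censors a participant without disability at the last successful test, including an adjudicated no-disability result. Protocol 10.2.1 likewise censors at the last evaluation of the primary outcome.

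The Particular cases paragraph of the same SAP section departs from both. Its trigger is: "In the case where more than 9 months are observed between two consecutive visits or between the last available visit and the death". What follows depends on the later result:

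- Criterion not met at the later visit: "then participants will be censored at the date of their first consecutive visit". If the gap starts at randomisation, the censoring time is 1 day.
- Criterion met, or death after the gap: "then the disability will be considered ascertained at the date of the first consecutive visit or at the date of the last available visit", with 183 days added.

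SAP 1.6 lists statistical modifications as not applicable. The only supportive analysis of the endpoint definition removes deaths (SAP 2.4.4.1). Reasons for censoring are tabulated by arm but not acted on.

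**The concern.** Two participants with the same gap are treated differently because of a result seen only when the gap ends. The one who fails contributes an event and six months at risk. The one who passes contributes nothing from the gap onwards, although the pass shows that he or she was still able to walk, and any later failure is ignored.

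This censoring is informative even when visits are missed purely at random. It raises the apparent hazard in each arm in proportion to that arm's gaps. If the arms differ in gaps, the primary hazard ratio and log-rank test shift against the arm that misses more. That test also gates the whole-population comparison.

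**Working it through.** **Inputs from the documents.** Protocol 10.1: "A total of 434 events are required to provide 85% power to detect a 25% reduction in the hazard", two-sided 5% log-rank test; 1,200 participants with SPPB below 8 accrued over 12 months; maximum follow-up 36 months; exponential dropout of 25% over two years. Allocation is 1:1 (protocol 7.4.3.2).

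**Assumed, because the documents are silent.** Rates of wholly missed visits from 5% to 20% per visit, missed at random; permanent disability; no deaths; unstratified analysis.

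**1. The plan's own figure.** Events = 4(z₀.₉₇₅ + z₀.₈₅)² / (ln HR)² = 4(1.960 + 1.036)² / (ln 0.75)² = 35.9 / 0.0828 = 434. It reproduces.

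**2. What triggers the rule.** From month 12 on, one wholly missed visit leaves about 12 months, for example month 6 to month 18: 548 − 183 = 365 days. A missed month 3 leaves six months and does not trigger it. A missed month 6 leaves 365 − 91 = 274 days, right at the nine-month limit.

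**3. The event rate inside a gap.** Take 100 one-year gaps and the annual risk of 19.9% that matches 434 events in 1,200 at HR 1, so about 20 failures.

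- SAP rule: 20 events over 20 × 0.5 = 10 person-years, or 2.0 per year. Only failers contribute time, half a year each, so the rate is 2.0 whatever the true hazard.
- Passers kept at risk: 20 events over 20 × 0.5 + 80 × 1 = 90 person-years, or 0.22 per year, which is the simulated hazard.

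**4. Simulation.** 1,500 trials per scenario, 600 per arm, with the accrual, follow-up and dropout above and visit dates varying with an SD of 0.3 months. Every missed visit is wholly missed. In the last two columns passers stay at risk and the 183-day dating of failures is kept.

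| True HR | Missed, MCI v HALE | SAP rule: HR | SAP rule: rejection | Kept at risk: HR | Kept at risk: rejection |
|---|---|---|---|---|---|
| 1.00 | 5% v 5% | 1.00 | 4.9% | 1.00 | 5.6% |
| 1.00 | 10% v 10% | 1.00 | 4.7% | 1.00 | 5.3% |
| 1.00 | 5% v 10% | 0.93 | 11% | 0.99 | 5.4% |
| 1.00 | 5% v 15% | 0.85 | 33% | 0.99 | 5.3% |
| 1.00 | 15% v 5% | 1.18 | 34% | 1.015 | 5.8% |
| 0.75 | 10% v 10% | 0.756 | 76% | 0.751 | 81% |
| 0.75 | 15% v 5% | 0.89 | 19% | 0.76 | 77% |

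With visits on exact nominal dates, a missed month 6 does not cross the limit. The 5% v 15% null case then gives an HR of about 0.90 and a type I error of 18-20%.

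**5. Allowing for phone and proxy visits.** Null case, 5% v 15% of clinic visits missed, with phone or proxy contact closing a share of the gaps (the share is assumed):

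| Share covered | HR | Type I error |
|---|---|---|
| none | 0.90 | 18% |
| 50% | 0.95 | 7.2% |
| 70% | 0.97 | 5.9% |
| 80% | 0.98 | 4.5% |

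**The case against.** The strongest reply is that the rule should seldom apply. Section 9.3.2 does ask participants to "attend clinic visits every twelve months", and a reader might infer that 12-month gaps are built in. The documents do not support that. The same section plans phone contact every six months, and telephone or proxy interviews where an in-person visit cannot be completed. SAP 2.1.3.1 adjudicates tests missed because a visit was held by phone or proxy. SAP 2.5.1 can date a visit from a proxy, PAT-D or outcome-events form. Such a visit closes the gap. This stands, and it makes the no-contact results a worst case.

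A reader might also infer unequal missed assessments from the contact schedules: twice a week at the centre for MCI, twice a month for HALE. Those are intervention sessions. The investigation schedule is the same in both arms (protocol 6.1), and people who stop attending sessions are still urged to attend assessments (9.3.6). Imbalance is plausible but not shown.

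The only data in the documents bearing on this, the counts under Figure S2 for SPPB 8-9, suggest modest losses. By the sixth column, participants removed without an event number 155 − 100 − 31 = 24 of 155 (15.5%) in MCI and 159 − 103 − 23 = 33 of 159 (20.8%) in HALE. These counts cover all causes in a secondary stratum, and the column times are not shown. They make a 15% wholly missed rate look high for that stratum. They do not show that the rule favoured MCI in the primary one.

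Finally, adding 183 days to date a failure is close to the midpoint of a 12-month gap (365 / 2 = 182.5), so that part of the rule is defensible. None of this justifies discarding an observed pass.

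**Conclusion.** The first bullet of the Particular cases rule is wrong as written. It conditions censoring on the later outcome and contradicts protocol 10.2.1 and the SAP's general rule without being listed as a change. It should be fixed, but it does not by itself invalidate the primary analysis.

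The mechanism rests on no assumption about why visits are missed; the size does. Without rates of visits missed by clinic, phone and proxy alike, neither the magnitude nor the direction of bias in this trial can be stated, and an HR of 0.85-0.90 or a type I error of 18-33% should not be read as an estimate for it. With phone or proxy cover of 50-80%, the same imbalance moves a null HR only to about 0.95-0.98. With equal missingness there is no bias under the null. The cost is then information: about 4-5 points of power at 10% missed (76% against 81%).

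The death part is secondary. A death more than nine months after the last visit is dated to a day on which the person was still alive, but deaths were not simulated and the effect is unquantified.

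**What to change.** Replace the first bullet in SAP 2.1.3.1, Particular cases, with:

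> If the walk is passed (or adjudicated no disability) at the later visit, the participant remains at risk through the gap and follow-up continues; censoring is at the last passed or adjudicated no-disability test.

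Then:

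- Record the change in SAP 1.6.
- Report gaps of more than nine months by arm.
- Add an interval-censored sensitivity analysis of the primary endpoint.
- As a secondary correction, date a death after a gap at the actual date of death, as the SAP's general rule does.
- Leave the 183-day dating of failures as it is.
- Reconcile the annual clinic visits in protocol 9.3.2 with the six-monthly visit table.

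Censoring passers and failers alike at the earlier visit is a weaker repair. In the null 5% v 15% case it gives an HR of 0.96 and keeps 181 + 147 = 328 events, against 192 + 178 = 370 under the SAP rule.

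The cost is SAP wording and a simpler derivation program before database lock, with no new data. The one downside is that a failure followed by recovery inside a gap goes unseen, as already happens between scheduled visits.

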# 1 OVERVIEW AND INVESTIGATIONAL PLAN

## 1.1 STUDY DESIGN AND RANDOMIZATION

The SPRINTT trial is a multicenter randomized controlled trial (RCT) involving a multicomponent intervention (MCI) (based on Physical Activity (PA) and nutritional counselling/dietary intervention, and information and communication technology [ICT] intervention) versus a healthy aging lifestyle education (HALE) programme in 1500 non-disabled, community-dwelling persons age 70 years and older with physical frailty and sarcopenia (PF&S) across nine European countries.

The eligibility of participants is established in a multi-step screening process. Participants are first screened by phone or mail, the phone interview/mail being designed to exclude individuals who are clearly ineligible or unlikely to benefit from participation in the study. Then, at the first clinic screening visit, medical and functional exclusions criteria are assessed. A second screening clinic visit is possible if medical information is considered insufficient at the first visit, in order to definitively determine the eligibility of the participant.

Each eligible participant is then randomized to one of the two interventions arms of the clinical trial (MCI or HALE group) using a ratio 1:1, with permuted-block randomization list through a centralized allocation system.

Randomization can only occur after all eligibility requirements have been met and all key baseline data have been entered in the SPRINTT application. Randomization is stratified by study site, gender, and SPPB category (i.e.,  $<8$  or  $\geq 8$ ). The algorithm has been designed to randomize 80% of patients with a SPPB category  $< 8$ .

Approximately 1500 participants (750 in each intervention arm) were expected to be recruited and randomized from approximately 17 sites in 11 European countries.

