### 1.3 DETERMINATION OF SAMPLE SIZE

The sample size calculation was based on the LIFE-M study database ([1](#), [2](#)). Specifically, survival analyses were run according to different levels of Short Physical Performance Battery (SPPB) score (lower than 8, versus 8 and 9). The outcome considered was major mobility disability (i.e. inability to complete the 400-m walk test). The effect of PA on major mobility disability was negligible in participants with a baseline SPPB score  $\geq 8$  (hazard ratio=0.94; 95% confidence interval [CI]: 0.72-1.23;  $p=0.65$ ). Conversely, the hazard ratio was statistically significant in participants with a baseline SPPB score lower than 8 (hazard ratio=0.75; 95%CI: 0.59-0.94;  $p=0.012$ ).

- A sample of 1,200 older persons with SPPB score  $< 8$  enrolled over 12 months is estimated to provide 85% power (434 events) to detect a 25% reduction in the hazard of major mobility disability over a maximum of 36 months of follow-up, considering an exponential dropout rate of 25% over 2 years and a log rank test with a 5% two-sided alpha level. An interim blinded sample size reassessment after 11 months from the beginning of recruitment allows taking immediate actions to preserve the study power in case the efficiency of enrolment or the number of observed events is not coherent with the original assumptions.
- In addition to not restrict the enrolment to older people with SPPB score lower than 8 that would jeopardize the aim of project to comprehensively characterize the PF&S condition and to not decrease the study power hence, the probability of success of the trial, it was decided to include in the study a convenience sample of 300 older adults with baseline SPPB score 8 or 9. An ad hoc hierarchical testing procedure has been formulated to control type I error: first, we will compare the effects of the

interventions in participants with SPPB score lower than 8 and, only in case of significant result (i.e., two sided  $p < 5\%$ ), the comparison will be extended to the whole study population

- At the first blinded sample size reassessment (may 2017) it was decided to increase the accrual period by 6 months, but maintaining a maximum of 36 months of follow-up period
- The last participant was randomized on November 15th 2017 (1205 in SPPB<8 stratum, 314 in SPPB 8-9 stratum)

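### The SAP's primary-endpoint rules contradict each other on a participant who dies during the study without any post-baseline visit: an event under one rule, censored at randomisation under another

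*Combined protocol and SAP*

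**What the plan says.** Three rules in SAP 2.1.3.1, under Derivation of primary endpoint, can reach a participant whose only visit is randomisation and who then dies.

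- **Date-of-death bullet.** Disability counts as ascertained "or at the date of death if the participants died during the study". No post-baseline visit is required.
- **Particular cases.** These apply when more than 9 months separate the last available visit from death. The wording that covers a participant seen only at randomisation reads "or the last available visit before to die) is the randomization visit, then the disability will be considered ascertained at the date"; the SAP sets that day at randomisation plus 183 days. The death is still an event; only its date changes.
- **Closing sentence.** "If no post-baseline visit is done, then participants will be censored at the date of randomization visit V1-T0". Death is not mentioned.

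The section does not say which rule takes precedence. The first scheduled post-baseline walk test is at Month 3.

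**The concern.** Whether such a participant is a primary event depends on which sentence the programmer applies. Under the closing sentence the participant stays in the randomised population but contributes no event and practically no follow-up. The endpoint otherwise counts deaths during the study, so the deaths at risk of being removed are mainly the earliest ones.

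Two things are at stake. The number of primary events is not fully defined. And if these deaths fall unevenly between arms, the choice moves the estimated effect. Protocol 8.6 has treatment codes released once the database is locked, so a choice left open until then could be made with the arms known.

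**Working it through.** **1. The rules side by side**, for a death during the study with no post-baseline visit:

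| Time of death | Date-of-death bullet | Particular cases | Closing sentence |
|---|---|---|---|
| Up to 9 months after randomisation | event at death | does not apply | censored at randomisation |
| More than 9 months after | event at death | event at day 183 after randomisation | censored at randomisation |

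In the first row one event rule conflicts with the closing sentence; in the second row two do.

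**2. Does another section settle it?**
- Protocol 10.1 and 10.2.1 define the endpoint by the walk test alone and do not count death, so they cannot break the tie.
- SAP 1.5 and 1.6 record no statistical change that would explain the rule.
- The supportive analysis in SAP 2.4.4.1 takes all deaths out of the event definition, so it does not show the effect of this choice.
- SAP 2.1.3.2 repeats the closing sentence for persistent mobility disability, but there death alone is not an event, so the same conflict does not arise.

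**3. Inputs for the size.** SAP 1.3 specifies "a log rank test with a 5% two-sided alpha level"; the sample "is estimated to provide 85% power (434 events) to detect a 25% reduction in the hazard of major mobility disability", "considering an exponential dropout rate of 25% over 2 years". It reports "1205 in SPPB<8 stratum, 314 in SPPB 8-9 stratum" as randomised. SAP 1.1 gives allocation "using a ratio 1:1, with permuted-block randomization list". Annual mortality *m* is not in the documents; I assume 2%, 4% and 6%.

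**4. The plan's own figure.** Schoenfeld: events = 4(1.960 + 1.036)² / (ln 0.75)² = 434. This matches the SAP.

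**5. Deaths before Month 3.** The dropout hazard is η = −ln(0.75)/2 = 0.1438 per year. Deaths before 0.25 years = 1205 × m/(m+η) × [1 − exp(−0.25(m+η))].
- m = 0.02: 5.9
- m = 0.04: 11.8
- m = 0.06: 17.6

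That is about 6, 12 and 18, or 1.4% (6/434) to 4.1% (18/434) of the target events.

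**6. Power if these events are lost.** Power = Φ(√d × |ln 0.75|/2 − 1.960).

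| Events lost | d | Power |
|---|---|---|
| 0 | 434 | 85.0% |
| 6 | 428 | 84.5% |
| 12 | 422 | 84.0% |
| 18 | 416 | 83.5% |

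**7. Imbalance, for illustration only.** With equal person-time and an event ratio of 0.75, 434 events split as 434/1.75 = 248 (HALE) and 186 (MCI).
- Five deaths removed from each arm: 181/243 = 0.745.
- Ten removed from MCI only: 176/248 = 0.71.
- Ten removed from HALE only: 186/238 = 0.78.

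The one-sided splits are extremes, not forecasts.

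**The case against.** The strongest reply is that a coherent reading already exists. The general censoring rule is for people who have not met the disability criterion, and death is listed as one way of meeting it. The closing sentence also has an ordinary purpose. Default censoring uses the last successful walk test, and the flowchart in SAP Appendix A places the baseline test at screening. A participant with no later visit would then usually get a censoring time of zero or less, so the sentence supplies a usable date for someone already due to be censored. And if it overrode the other rules, the Particular cases wording on a death whose last visit is randomisation would have no effect.

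Most of this stands as evidence of intent. It does not remove the contradiction, because the sentence as written covers everyone without a post-baseline visit.

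Stronger readings that the documents do not support:

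- **The last sentence overrides because it comes last.** No such order is stated, and it is the less natural reading.
- **Early deaths are events under two sentences.** Within 9 months only the date-of-death bullet applies.
- **Later deaths among early dropouts add several more cases.** Withdrawing participants are offered an end-of-study visit (Protocol 7.3). SAP 2.1.3.1 treats phone and proxy contacts as visits, and SAP 2.5.1 lets the ADL Proxy or Outcome events form supply a visit date. SAP 2.1.4.3 ends the death observation period with study participation. Such deaths cannot be counted from the documents.
- **Early deaths, or harm from early exercise, would be hidden.** SAP 2.4.5.3 analyses mortality separately in the SPPB <8 population, with a stratified log-rank test and a hazard ratio. Protocol 7.4.3.1 also allows two months from randomisation to the first individual intervention, so some of these deaths could come before any exercise.

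**Conclusion.** Wrong as written: the rule contradicts itself. A death during the study with no post-baseline visit is an event under the date-of-death bullet and, after more than 9 months, under the Particular cases text as well. It is censored at randomisation under the closing sentence. The +183-day text points to events as the intent, but intent has to be inferred.

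The numerical effect is probably small: about 6 to 18 deaths before Month 3, and a loss of about 0.5 to 1.5 points of power. This assumes constant mortality of 2% to 6% per year from randomisation, the plan's dropout rate, no visit before Month 3, and an otherwise full 434 events. For deaths before Month 3 it is an upper range, because entry criteria exclude people with short life expectancy or severe disease. Later deaths with no visit at all would come on top, but the documents give no basis for a number. The case for correction rests on an undefined event status in the primary endpoint and on possible imbalance between arms, not on power.

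**What to change.** Replace the closing sentence of the derivation in SAP 2.1.3.1 with, for example: *A participant who has no post-baseline visit and is not known to have died during the study is censored at the randomisation visit; deaths during the study follow the rules above.*

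In the supportive analysis that excludes deaths (SAP 2.4.4.1), state that participants who die with no post-baseline visit are censored at randomisation. Its present formula would date them from the screening walk test.

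The cost is one reworded SAP sentence and one clarifying clause, settled before treatment codes are released. No data collection changes, and the 434-event basis stays as it is.
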